### Sample measurement

G*Power 3.1.9.2 was used to perform the power calculations. The change of Cobb angle was the primary outcome measurement. The results of our previous study showed that the change of Cobb angle in the experimental group was − 1.55 ± 4.39 degrees, whereas in the control group, it was 2.90 ± 2.60 degrees [25]. The α will be 0.05, and the β will be 0.05. Therefore, we should recruit 19 patients to each group. Considering 10% potential attrition, 21 patients per group will be recruited.

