### Data collection, data management, and statistical analysis plan

The primary outcome is the change of Cobb angle, and the secondary outcome measures will include the ATR, sagittal index, and quality of life. Descriptive statistics will be calculated for baseline demographics, physical examination, radiographs, and questionnaire data, and results will be presented as the mean ± SD, whereas categorical variables will be expressed as percentages. The chi-squared test will be used to compare the categorical/dichotomous variables. Separate analyses will be conducted for each outcome.

Data will be entered using EpiData software designed for this study. All data will be collected, typed, and analyzed by a masked statistician who will not have access to study assignment. The main investigators will check the data every 2 weeks to ensure the quality.

The primary endpoint is the pre- and posttreatment difference in the Cobb angle. We have calculated that a sample size of 21 patients per group would be capable of detecting a between-group difference of 5 degrees in the primary endpoint with a type I error of 5% and a power of 95% [20]. Because the interval of Cobb angles at entry is 10–20 degrees, and assuming a uniform distribution of Cobb angles in this range (the most unfavorable scenario), an SD of 5 degrees is estimated [8].

Baseline comparability will be assessed using Student’s *t* test for independent samples. To screen for variables associated with each of the outcome variables, univariate linear mixed models for each relevant covariable (age, gender, body mass index, Risser sign, time since menarche, apex levels, curve pattern, and compliance may have associations with risk of progression) will be conducted.

Multiple linear mixed models for each time point will be tested, including covariables found significant at *p* ≤ 0.20 in the univariate analysis, and after screening for multicollinearity [42].

For the ordinal outcome (SRS-22, which is based on only one item with five levels), generalized linear mixed effects model analysis will be used.

Furthermore, because subjects with younger than 13 years of age are characterized by a higher risk of progression [43], the patients will be divided into two subgroups (age < 13 years and age ≥ 13 years), and a linear mixed model analysis for the primary outcome will be performed on each subgroup.

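### Separate primary-outcome models in patients under 13 and 13 or over describe each age group but cannot show whether the treatment effect differs by age

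*Protocol article*

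**What the plan says.** The section on data collection, data management and statistical analysis says that "the patients will be divided into two subgroups", with the cut at 13 years, and that "a linear mixed model analysis for the primary outcome will be performed on each subgroup". The reason given is prognostic: "because subjects with younger than 13 years of age are characterized by a higher risk of progression".

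The article states no treatment-by-age interaction, no direct comparison of the two subgroup effects and no exploratory label. Elsewhere in the analysis section, age appears only in the list of candidate covariables for univariate screening. That is a main effect and says nothing about whether the treatment effect varies with age.

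**The concern.** Whether an effect differs between two groups is a question about the difference between two estimates. Fitting the model once in each group tests each estimate against zero and never tests them against each other. With about 10 patients per arm in each model, a true effect of the size the trial was designed for will quite often reach significance in one group and miss it in the other.

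Because the split is introduced by a contrast between age groups and applied to the primary outcome, readers will naturally set the two results side by side. What is at stake is a conclusion that the exercise programme works only in younger, or only in older, patients when the data show no such thing.

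**Working it through.** **Inputs.** From Sample measurement: "the change of Cobb angle in the experimental group was − 1.55 ± 4.39 degrees" and "in the control group, it was 2.90 ± 2.60 degrees"; "The α will be 0.05, and the β will be 0.05"; "we should recruit 19 patients to each group", raised to 21 for attrition. From the analysis section: an alternative pair of inputs, a 5-degree difference and an SD of 5 degrees. Allocation is 1:1. The age split is not given; I take it as even and then vary it.

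**Reproducing the plan's figure.** Difference = 2.90 − (−1.55) = 4.45. Pooled SD = √((4.39² + 2.60²)/2) = 3.61. d = 4.45/3.61 = 1.233. A two-sided two-sample t test (noncentral t) has 94.9% power with 18 per group and 95.9% with 19, so the stated 19 is reproduced.

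The alternative inputs give d = 5/5 = 1.0. With 21 per group, two-sided power is then 88.5%, not the stated 95%. That is a separate matter; I use these inputs here only as a second scenario.

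**Power within one age group.** For arm sizes n₁ and n₂, the noncentrality is d/√(1/n₁ + 1/n₂) with n₁ + n₂ − 2 degrees of freedom. If the true effect is the same in both groups, P(exactly one significant) = p₁(1 − p₂) + p₂(1 − p₁), which is 2p(1 − p) for an even split.

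| Even split | Arms per age group | Pilot inputs: power | Exactly one significant | 5 degrees, SD 5: power | Exactly one significant |
|---|---|---|---|---|---|
| 42 analysed | 10 and 11 | 76.4% | 36.1% | 58.4% | 48.6% |
| 38 analysed | 9 and 10 | 71.6% | 40.7% | 53.7% | 49.7% |
| 36 analysed | 9 and 9 | 69.1% | 42.7% | 51.3% | 50.0% |

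Worked example, 38 analysed, pilot inputs: 2 × 0.716 × 0.284 = 0.407.

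**Sensitivity.**
- Simulation with the two unequal pilot SDs (40,000 runs): 39.6% with 38 analysed and 35.8% with 42.
- 30:70 age split: 54.1% (38) and 48.1% (42) on the pilot inputs; 57.5% and 55.9% on 5 degrees, SD 5.
- 20:80 age split: 64–67% across both sets of inputs.
- A larger standardised effect lowers the figure. Combining 5 degrees with SD 3.61 gives 30.6% (38) and 25.1% (42) at an even split.
- No true effect: 2 × 0.05 × 0.95 = 9.5%. The chance of at least one significant subgroup is 1 − 0.95² = 9.75%.

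**What an interaction term would deliver.** With an even split there are four cells of N/4 patients. SE of the interaction = SD × √(4/(N/4)), on N − 4 degrees of freedom.
- SD 3.61, N = 38: SE = 3.61 × √(4/9.5) = 2.34, 95% CI half-width 4.8 degrees. N = 42: half-width 4.5 degrees. Power for a 4.45-degree difference between the stratum effects: 46% and 50%.
- SD 5: half-width 6.6 (N = 38) and 6.2 (N = 42) degrees. Power for a 5-degree difference: 32% and 35%.

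By construction, the interaction test wrongly signals a difference in 5% of trials when the effect is the same at all ages.

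**The case against.** The strongest reply is that the protocol never says it will claim an age-dependent effect. Its reason for the split is prognostic, and its objectives, primary hypothesis and discussion make no age-specific claim. That is correct, and separate estimates are acceptable as description. A reader might infer that the trial plans to declare exercise effective in one age group only; the text does not say so. What stands is narrower: the stated method yields no valid comparison if anyone makes one.

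A second reply is that a condensed article may leave an interaction term and an exploratory label to a fuller plan. Their absence alone would be no finding. But the article fixes the method, separate models, and that method can be judged as written.

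Three stronger readings should be set aside.
- A reader might infer that a chance result would favour the under-13s because they are the higher-risk group. With equal effects and an even split, discordance is symmetric. With an uneven split the larger group is more often the significant one, and the document does not say which that is.
- A reader might take each model's own residual variance as an error. If younger patients progress more, variance may well differ by age, and separate models allow for that.
- A reader might take 40–50% as an unconditional rate. It depends on the true effect, the age split, and reading each model as a significant or non-significant verdict, which the article does not prescribe.

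The low power of the interaction is a fair point too. It shows how little 42 patients can say about age, and an interval makes that visible.

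**Conclusion.** The point holds in a limited form. The stated subgroup analysis can describe the effect in each age group but cannot show whether it differs by age. Discordant results between the groups would be common even with one common effect: about 36–43% on the pilot inputs (36–41% with 42 down to 38 analysed; 43% needs the count to fall to 36) and about 49–50% on 5 degrees with SD 5.

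These figures assume a true effect equal to the design effect in both groups, a roughly even age split, and unadjusted two-sided t tests standing in for the planned mixed models. Covariate adjustment could shift them somewhat. The method point depends on none of these assumptions. The main primary analysis and the sample size are untouched, so this is a cheap improvement, not a flaw that threatens the trial.

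**What to change.** Replace the two models with one fitted to all patients, containing arm, age group (under 13, or 13 and over) and their interaction. Residual variance may be allowed to differ by age group if the investigators wish. Report the interaction estimate with its 95% CI and, from the same model, the treatment effect in each age group with its CI. Label the analysis exploratory, make no significance claims within subgroups, and state beforehand that the interaction has low power.

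The cost is a change of wording and one model in place of two, with no extra patients or data. The price is an interval likely to be about as wide on each side as the design effect itself, so the analysis will seldom settle the age question.

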### Interim analysis

An interim analysis will be performed on the primary endpoint of Cobb angle when enrolling 20 patients, including control group and experimental group, by a single statistician who is blinded to allocation and reports the results to the main investigators. The main investigators will discuss the results of the interim analysis with the monitoring board. In this study, the change of Cobb angle is the only primary outcome measurement; the secondary outcome measurements are the supporting elements for the whole outcome.

Our primary hypothesis is that the experimental intervention of three-dimensionally integrated exercise for scoliosis will optimize improvement in outcome effects (reduction in Cobb angle and improvement in multifidus activation). Effect sizes will be estimated using Cohen’s *d*, which corresponds to the mean difference between the groups in the change observed from baseline to 6 months (three-dimensionally integrated exercise for scoliosis standard of care), divided by the pooled SD at baseline (Cohen’s *d* ≥ 0.8 = large, 0.5–0.8 = moderate, 0.2–0.5 = small [45]). According to the previous study, the perceived mean global rating of change in the specific exercise group was 3.8 ± 2.2, corresponding to moderate improvement, and 0.3 ± 1.7 in the standard care group, corresponding to a small amount of deterioration [46]. In this study, an effect size change of 0.3 would be considered a significant finding to stop the study when performing the interim analysis [47]. The reasons for withdrawal from trial by arm will be calculated by the physical therapist.

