**Methods/design:**

The study is designed as a randomized controlled trial. Participants include 42 patients with AIS aged 10–16 years. Randomly assigned patients will follow a 6-month treatment, either in a control group with standard care of observation following the Scoliosis Research Society criteria or in an experimental group with three-dimensionally integrated exercise for scoliosis. Blinded assessments at baseline and immediately after intervention will include the change of Cobb angle, angle of trunk rotation, sagittal index, and quality of life.

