### Data monitoring and auditing

A monitoring board, including independent assessors (not involved in the study) from the Shanghai Jiao Tong University School of Medicine, will review all data and can conduct an audit of the trial at any time.

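### Interim results go to the main investigators before the monitoring board, so the investigators may learn the between-group difference while recruitment or follow-up continues

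*Protocol article*

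**What the plan says.** The Interim analysis section plans one analysis of the Cobb angle, "when enrolling 20 patients, including control group and experimental group". It is done "by a single statistician who is blinded to allocation", who "reports the results to the main investigators". The next step is: "The main investigators will discuss the results of the interim analysis with the monitoring board". This is the only route to the board that the section describes.

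Two rules act on the result:

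- **Effect size.** The same section says that "an effect size change of 0.3 would be considered a significant finding to stop the study when performing the interim analysis". It defines the effect size as a Cohen's d for the difference between the groups in 6-month change.
- **Failures.** Suspension criteria ends the trial if failures exceed 40% in one group or the other.

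Other sections bear on who knows what:

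- Randomization and masking says that therapists and patients are not blinded and that the evaluator is.
- The Discussion names the assessor, the enrolment assistant and the statisticians as blinded. It does not name the main investigators.
- Data collection, data management, and statistical analysis plan says: "The main investigators will check the data every 2 weeks to ensure the quality".
- Confidentiality gives database access to the main investigators alone.
- Data monitoring and auditing describes a board that includes assessors from outside the study and that may review all data.

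**The concern.** A monitoring board protects a running trial by holding the comparative results so that those who run it need not see them. Here the order is reversed: the trial team receives the results and brings them to the board. No section withholds the comparison from the investigators.

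The treatment is behavioural and is delivered openly. A team that knows how the comparison stands can, without intending to, present the trial differently at consent, press harder or less hard for compliance, or handle a wavering family differently. The investigators also enter the stopping discussion already knowing the answer. Any of these could bias the primary comparison, and all are avoidable because the board already exists.

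**Working it through.** **1. Do the results have to be by group?** The report is not described as being by arm, so this must be inferred from the rules it serves. A between-group Cohen's d cannot be computed from pooled data. A rule that looks for more than 40% failures in one group or the other cannot be applied to pooled data either. The report must therefore contain group-level results. It need not name the groups, because the statistician is blinded and could label them A and B.

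**2. Would coded labels hide the direction?** The inputs are in Sample measurement: changes of −1.55 (SD 4.39) and 2.90 (SD 2.60) degrees.

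- Difference: 2.90 + 1.55 = 4.45. Pooled SD: √((4.39² + 2.60²)/2) = 3.608. Standardised difference: 4.45/3.608 = 1.233.
- A two-sided t test at α = 0.05 and power 0.95 gives 19 per group, the plan's own figure. With its attrition allowance the plan has 21 per group, 42 in all.
- Assume 10 patients per group with outcomes at the interim. Standard error: 3.608 × √(2/10) = 1.61.
- Chance that the group with the better mean is the experimental one: Φ(4.45/1.61) ≈ 0.997 under the planned effect, Φ(2.225/1.61) ≈ 0.92 under half of it, and 0.5 under no effect.

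Coding hides direction only if the true effect is small.

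**3. How often would the trial continue under the planned effect?** The effect size is divided by the baseline SD. The plan states 5 degrees; a uniform spread over 10–20 degrees gives 10/√12 = 2.89. The observed difference needed for 0.3 is 0.3 × 2.89 = 0.87 or 0.3 × 5 = 1.5 degrees. The chance of exceeding it is Φ((4.45 − 0.87)/1.61) ≈ 0.99 or Φ((4.45 − 1.5)/1.61) ≈ 0.97.

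**4. How many patients are still to be randomised?** On the literal trigger, (42 − 20)/42 = 22/42 = 52%. However, the endpoint is the 6-month change, so 20 outcomes cannot exist when the 20th patient enrols. No recruitment rate is given. Assume a steady rate of r patients per month and no dropout:

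| Assumed r | Outcomes available when the 20th enrols (20 − 6r) | Still to be randomised when 20 outcomes exist (22 − 6r) |
|---|---|---|
| 1 | 14 | 16 |
| 2 | 8 | 10 |
| 22/6 ≈ 3.7 or more | 0 | 0 |

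Very slow recruitment leaves the last column near 22, so its range is 22 to 0. Those of the 22 who have been randomised by then are in follow-up.

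**5. Which routes to bias are closed?**

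| Route | Safeguard in the protocol |
|---|---|
| Measurement of the Cobb angle | Blinded evaluator |
| Invitation | Assistant blinded to the randomisation |
| Allocation | Numbered, opaque, sealed envelopes |
| Consent discussion | None stated; a clinic physician explains the trial |
| Encouragement to comply | A 70% trigger, handled by an unblinded therapist |
| Withdrawal | At the family's request; individual suspension rests partly on clinical examination |
| Decision to stop | Investigators see the results first |

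The protocol does not say whether the main investigators overlap with the consenting physician or the therapists.

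**The case against.** The best defence has four parts.

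- **Blinded statistician.** A reader might infer that results by named arm are handed over. The text does not say so, and the report may carry only codes. This stands as a limit on the claim, but step 2 shows that codes give little cover if the effect is near the planned one.
- **Extent.** A reader might infer that 52% to 100% of the trial is exposed. The protocol does not support that range. If the analysis is run at the 20th enrolment, there may be few or no outcomes to disclose. If it waits for 20 outcomes, recruitment may be over. Nor can all of the trial be affected, since a difference exists only once some patients have finished.
- **Stopping rule.** Under the planned effect, 0.3 is exceeded about 97% to 99% of the time, so the case in which codes are easily broken is mostly one in which the trial stops. Because the threshold is published, a reply of continue is also informative. Both points reduce the harm. Neither removes it: continue does not give the size or direction of the difference, and the investigators would still be taking part in the stopping discussion with the result in hand.
- **Safeguards.** The blinded evaluator, blinded assistant and concealed envelopes close three routes. The others in step 5 remain open.

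A reader might also take the two-weekly data check as proof that the investigators compare the groups. It is described as a quality check and proves no such thing. It matters only because nothing keeps allocation out of it.

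**Conclusion.** The point holds as a weakness in the reporting route that the protocol fixes. The main investigators receive the interim results first, the results must be by group, and nothing withholds the comparison from the investigators. They may therefore learn the difference, perhaps from coded groups, before recruitment or follow-up has finished.

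The number still to be randomised is 22 of 42 (52%) on the literal trigger, and between 22 and 0 if 20 six-month outcomes are awaited. The figures for decoding the groups rest on the planned effect and an assumed 10 patients per group. This is a risk of bias, not a demonstrated bias, and the sample size does not change. The change is worth making because it costs almost nothing.

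**What to change.** - **Interim analysis section:** state that the statistician sends the group-level interim results only to the independent members of the existing monitoring board. Those members hold the group code and return only a continue or stop recommendation to the main investigators.
- **Data collection, data management, and statistical analysis plan, and Confidentiality:** state that the main investigators' data checks and database access exclude allocation and any outcome summary by group until the data are locked after the last 6-month visit. Without this, rerouting the report would not keep the comparison from those who alone have database access.
- **Useful alongside:** say whether the 20 patients are those enrolled or those with a 6-month outcome, so that the exposure can be sized.

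The cost is a few sentences and keeping allocation out of the data that the investigators can see. No patients or visits are added, and the board already exists. The small downside is that the investigators do not see the interim estimate.

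### The interim rule would stop the trial on an observed effect size of 0.3 in 20 patients, a threshold that chance alone crosses in favour of exercise in roughly 18 to 30% of trials

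*Protocol article*

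**What the plan says.** All of the following is in the protocol article.

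- **Interim analysis, timing.** One look at the Cobb angle is planned "when enrolling 20 patients, including control group and experimental group". Allocation is 1:1 (Randomization and masking), so about 10 per arm.
- **Interim analysis, measure.** Cohen's d is the between-group difference in change from baseline to 6 months, "divided by the pooled SD at baseline". The same paragraph labels values from 0.2 to 0.5 as small.
- **Interim analysis, rule.** "an effect size change of 0.3 would be considered a significant finding to stop the study". No direction is given. Cohen's d is the only effect size the section defines.
- **Interim analysis, reporting.** A statistician blinded to allocation "reports the results to the main investigators", who then discuss them with the monitoring board.
- **Sample measurement.** "The α will be 0.05, and the β will be 0.05". The planning data are that "the change of Cobb angle in the experimental group was − 1.55 ± 4.39 degrees" and "in the control group, it was 2.90 ± 2.60 degrees". "Therefore, we should recruit 19 patients to each group", raised to 21 for attrition.
- **Data collection, data management, and statistical analysis plan.** 5% type I error and 95% power are restated for 21 per group, a 5-degree difference and an estimated SD of 5 degrees.
- **Suspension criteria.** Clinical significance at the interim is a 5-degree Cobb change, described as the reliability of the radiograph. A separate rule ends the trial if more than 40% of patients fail in either arm.

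**The concern.** The section fixes a number that decides whether the trial continues, and that number is far too small for 20 patients. By the protocol's own labels 0.3 is a small effect, yet the trial is planned around a large one. A rule this loose is likely to be met by chance when exercise does nothing. It is almost certain to be met when exercise works as planned. Either way the trial would tend to end at about half its size, with a wide interval for the Cobb difference, and the design error rates quoted for 21 per group would no longer describe it.

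Two features make this worse. The look is triggered by enrolment although the endpoint is a 6-month change, so some of the 20 may have no outcome yet. And the interim result goes to the investigators who run the trial before the board discusses it.

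**Working it through.** **Inputs.** From Sample measurement: changes of −1.55 (SD 4.39) and 2.90 (SD 2.60); two-sided α 0.05, power 0.95. From Interim analysis and the 1:1 ratio: 10 per arm, threshold 0.3 baseline SD. The documents give no observed baseline SD, so a range is assumed: 10/√12 = 2.89 (uniform over the 10 to 20 degree entry window) up to the 5 degrees stated in the analysis section. The value 5 is the most that window allows, with half the patients at each limit.

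**1. The plan's own sample size.** Difference = 2.90 + 1.55 = 4.45. Pooled SD of change = √((4.39² + 2.60²)/2) = 3.61. d = 4.45/3.61 = 1.23. A two-sided two-sample t test (noncentral t) needs 19 per group, with power 95.9%. The stated 19 is reproduced. With 21 per group analysed, power is 97.4%.

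**2. What 0.3 means at the look.** With baseline SD equal to SD of change, t = 0.3 × √(10/2) = 0.67 on 18 df, two-sided p = 0.51. In degrees, 0.3 × 2.89 = 0.9 and 0.3 × 5 = 1.5. On the rule's own scale the planned 4.45 degrees is 4.45/5 = 0.89 to 4.45/2.89 = 1.54, three to five times the threshold.

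**3. Chance of crossing in favour of exercise with no true effect.** P = 1 − Φ(0.3 × SD_baseline / (SD_change × √(2/10))).

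| SD of change | Baseline SD | Argument of Φ | P |
|---|---|---|---|
| 3.61 | 2.89 | 0.54 | 29.6% |
| 3.61 | 5 | 0.93 | 17.6% |
| 5 | 2.89 | 0.39 | 34.9% |
| 5 | 5 | 0.67 | 25.1% |

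Simulation (200,000 trials per setting) agrees: about 30% and 18% for SD of change 3.61, and 35% and 26% for SD of change 5.

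**4. Fewer complete patients.** With equal SDs, P = 1 − Φ(0.3 × √(n/2)): 25% at 10 per arm, 32% at 5 and 36% at 3.

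**5. Operating characteristics under the two readings** (simulated, 10 per arm at the look, 21 at the end; ranges run over baseline SD 2.89 to 5; SD of change 3.61 under no effect, 4.39 and 2.60 under the planned effect).

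| | (a) Stop is the positive result | (b) Stop is followed by a 5% t test |
|---|---|---|
| No effect | Declared in favour of exercise: 19 to 30% (nominal 2.5%) | Two-sided type I error: 5.2 to 5.6% |
| 4.45 degrees | Power: about 99% | Power: 75 to 77% |

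At 4.45 degrees the rule is met at the look in 96.5 to 98.7% of trials. Power under (b) is therefore close to that of a t test with 10 per arm, which is 74%.

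**6. A strict boundary for comparison.** Two-sided p < 0.001 on 18 df needs |t| ≥ 3.92, so d ≥ 3.92/√5 = 1.75 on the SD of change, about 1.75 × 3.61 = 6.3 degrees. With the final test at 0.05, simulated overall type I error is about 5% and power with 21 per arm about 97%. The boundary is crossed in about 18 to 19% of trials at 4.45 degrees.

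**The case against.** A reader might infer that type I error and power are both lost at once. They are not: the two losses belong to different readings. The wording, which treats 0.3 as a finding in itself, favours reading (a), where power is high. Under (b) type I error is nearly kept.

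The rule may also not be automatic. The results are discussed with a monitoring board that includes independent assessors, and the phrasing can be taken as guidance. So the stopping frequencies are those of the rule applied as written, not a forecast. This stands, but it does not make 0.3 a sound guide.

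The percentages rest on assumptions. The SD of change comes from the sponsor's earlier work, which the Background lists among 3-month studies, whereas this endpoint is at 6 months. The baseline SD is a range. Complete data are assumed for all 20 patients, though the timing makes that doubtful. A larger SD of change or fewer complete patients would raise the chance of a false stop.

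Two stronger readings are not supported. The text does not say that results unblinded by arm reach the investigators, and coded groups are possible; but a between-group effect size still shows the trend. Nor does it give a direction for the stop, so only crossings in favour of exercise are counted here.

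Finally, how α is divided between looks may be left to an analysis plan that is not shown, and that silence is not the fault. The fault is the stated threshold. The 5 degrees in Suspension criteria concerns change in a patient, so comparing it with a group difference shows scale only; the analysis section does, however, also use 5 degrees as the between-group difference to detect.

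**Conclusion.** The concern holds in this form: 0.3 at a 20-patient look is a wrongly chosen stopping threshold, not a detail left for later. It corresponds to p of about 0.51 and to 0.9 to 1.5 degrees. Chance would cross it in favour of exercise in about 18 to 30% of trials with an SD of change of 3.61, or 25 to 35% with an SD of change of 5, given complete outcomes in 10 per arm.

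The stated pair of 5% and 95% survives under neither reading: (a) breaks the first figure and (b) the second. The exact percentages depend on SDs that the documents do not report. The conclusion does not, because no baseline SD possible within the entry window brings the chance of a false stop near 2.5% at either SD of change considered. This should be corrected before the interim look is taken.

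**What to change.** - **Threshold.** Delete the efficacy stop at 0.3. Having no efficacy stop is simplest for 42 patients with a 6-month endpoint. If one is wanted, use a Haybittle-Peto boundary: two-sided p < 0.001 on the change in Cobb angle (about d ≥ 1.75 on the SD of change at 10 per arm), with the final test kept at about 0.05.
- **Timing.** Take the look when 20 patients have their 6-month radiograph, not when 20 are enrolled.
- **Reporting.** Send the interim comparison to the existing monitoring board, which tells the investigators only to continue or stop.
- **Consistency.** Reconcile the Interim analysis section with the separate 40% failure rule in Suspension criteria, so that it is clear which rules apply at the look.

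The cost is a change of protocol wording; the sample size is unaffected. The downside is that early stopping for benefit becomes unlikely: about 18 to 19% at the planned effect with the strict boundary, and none if the efficacy stop is dropped.
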